## Abstract

**Background:**

Missed injury is commonly used as a quality indicator in trauma care. The trauma tertiary survey (TTS) has been proposed to reduce missed injuries. However a systematic review assessing the effect of the TTS on missed injury rates in trauma patients found only observational studies, only suggesting a possible increase in early detection and reduction in missed injuries, with significant potential biases. Therefore, more robust methods are necessary to test whether implementation of a formal TTS will increase early in-hospital injury detection, decrease delayed diagnosis and decrease missed injuries after hospital discharge.

**Methods/Design:**

We propose a cluster-randomised, controlled trial to evaluate trauma care enhanced with a formalised TTS procedure. Currently, 20 to 25% of trauma patients routinely have a TTS performed. We expect this to increase to at least 75%. The design is for 6,380 multi-trauma patients in approximately 16 hospitals recruited over 24 months. In the first 12 months, patients will be randomised (by hospital) and allocated 1:1 to receive either the intervention (Group 1) or usual care (Group 2). The recruitment for the second 12 months will entail Group 1 hospitals continuing the TTS, and the Group 2 hospitals beginning it to enable estimates of the persistence of the intervention. The intervention is complex: implementation of formal TTS form, small group education, and executive directive to mandate both. Outcome data will be prospectively collected from (electronic) medical records and patient (telephone follow-up) questionnaires. Missed injuries will be adjudicated by a blinded expert panel. The primary outcome is missed injuries after hospital discharge; secondary outcomes are maintenance of the intervention effect, in-hospital missed injuries, tertiary survey performance rate, hospital and ICU bed days, interventions required for missed injuries, advanced diagnostic imaging requirements, readmissions to hospital, days of work and quality of life (EQ-5D-5 L) and mortality.

**Discussion:**

The findings of this study may alter the delivery of international trauma care. If formal TTS is (cost-) effective this intervention should be implemented widely. If not, where already partly implemented, it should be abandoned. Study findings will be disseminated widely to relevant clinicians and health funders.

**Trial registration:**

ANZCTR: ACTRN12613001218785, prospectively registered, 5 November 2013

**Electronic supplementary material:**

The online version of this article (doi:10.1186/s13063-015-0733-y) contains supplementary material, which is available to authorized users.

## Background

Missed injuries after multi-trauma are a significant health problem, affecting young to middle-aged adults (mainly men). Estimates of incidence are highly variable, but most likely between 1 to 5% of all trauma patients have missed injuries [1,2]. Missed injury is a common quality indicator in trauma care [3,4] and can be the result of several factors, including the prioritisation that takes place during the initial assessment in the Emergency Department (ED), quality of the assessor and institution-specific processes.

The standard primary and secondary surveys by ED, intensive care unit (ICU) and surgical teams have been shown to miss injuries [1,2,5,6]. Performance of a trauma tertiary survey (TTS) has been suggested as a tool to address this problem and minimise the risk of missed injuries. [5] The TTS should follow the episode of emergency care (primary and secondary survey and emergency interventions). It comprises a comprehensive general physical re-examination and review of all investigations, including diagnostic imaging and blood results, within 24 hours [6-8] and again when the patient is conscious, cooperative and mobilised. [5,8,9].

The TTS would be expected to reduce missed injuries and therefore improve trauma care. However, our recent systematic review [2] found sub-optimal evidence to support this.

Among the deficiencies was the substantial variation in outcome definitions for missed injury, leading to a recommendation for a classification (See Table 1). No study reported on missed injury rates after hospital discharge (Type III) or functional (long-term) outcomes. [5,7-14]

**Table 1 Tab1:** **Missed injury classification** [2]

**Missed injury Type: (delay of)**	**Description**
Type I ≤ 24 hours)	***Before trauma tertiary survey (TTS), or as result of TTS - in-hospital:***
	Injury missed at initial assessment (primary and secondary survey and emergency intervention), but detected within 24 hours, before or through formal TTS.
	(that is, injury missed at initial assessment)
Type II (>24 hours)	***After TTS, in-hospital:***
	Injury missed by TTS, detected in hospital after 24 hours.
	(that is, injury missed at initial assessment *and* TTS,)
Type III (After hospital discharge)	***After TTS, after hospital discharge:***
	Injury missed during hospital stay including TTS,
	(that is, injury missed at initial assessment *and* TTS *and* hospital stay)

A retrospective study [15] in our Australian level II trauma facility found poor compliance to routine TTS and identified a lack of data regarding post-discharge missed injuries. A subsequent, pragmatic, prospective before-and-after study [16] evaluated the implementation of a formalised TTS procedure by measuring missed injury rates during a hospital stay (Type I and II) as well as after discharge (Type III). The in-hospital missed injury rate (Type I and II combined) was similar for both groups (Pre: 3.8% versus Post: 4.8%), as were Type III missed injuries at 1 month (Pre: 13.7% versus Post: 11.5%), and 6 months (Pre: 3.8% versus Post: 3.3%). Although there was a substantial increase in tertiary survey performance (27% versus 42%, *P* < 0.001), this may not have been enough to detect any potential differences in missed injury rates if they exist.

Missed injuries may be minor or only require conservative treatment. Therefore, the focus ideally should be on clinically significant missed injuries. Few studies have defined ‘clinically significant’ *post hoc*, [7,11,12] with most studies not providing any definition. Whilst the incidence of clinically significant missed injuries is unknown, they are more likely to lead to prolonged morbidity or mortality. Although mortality as a result of missed injuries is conceivably rare, our prospective study indicated that approximately 1% of the cohort required a surgical intervention for injuries detected after the hospital discharge. [16].

Current international guidelines such as Early Management for Severe Trauma (EMST) do mention consideration of tertiary surveys, but do not mandate or formalise their implementation. [17] This may be the result of their focus on *early* trauma care, where the tertiary survey by can be conducted up to 24 hours after ED assessment.

There are a number of potential concerns regarding performing a formalised TTS on every multi-trauma patient. It will take more medical and nursing staff time to perform, and may lead to over-investigation. It could lead to over-diagnosis by labelling minor self-limiting conditions with subsequent patient concern or overconsumption of medical resources. As such, it may feed the notion that even minor, self-limiting injuries should always be diagnosed and actively managed. Additionally, re-examination by the same clinician or team may miss the same injury twice due to systematic error or persistent cognitive error. Ultimately, the decision to implement a formalised TTS procedure relies on the assessment of the clinical effect, as well as the value of the clinical benefits, compared to the associated change in costs. However, in order to provide an evaluation of the cost-effectiveness of a formalised TTS, reliable estimates of the effectiveness of a formal TTS is a necessary requirement.

In summary, questions remain regarding the utility and (cost-) effectiveness of the TTS. Although there is a sound rationale for performing formalised TTS, the current data is inconclusive since the quality of data is low and effect size variable. The health care costs to provide this extra layer of safety-net may not prove cost-effective. This protocol specifies the design for a multicentre clinical trial to assess the effectiveness and feasibility of implementing a formal TSS. The results of the study will provide high level evidence that either a TTS should be mandatory in trauma patients, or that we can save resources if no benefit is found.

### Aims and hypotheses

Our primary aim is to determine whether the implementation of a formalised TTS will decrease missed injuries post hospital discharge (Type III injuries) and, as secondary aim, increase injury detection in hospital (Type I and II injuries combined). We further hypothesise that the intervention effect will be maintained and that the intervention would lead to decreased clinically significant missed injuries as judged by a blinded expert panel, decreased hospital and ICU bed days, decreased readmissions to hospital, improved quality of life and decreased time off work. We expect complications of the injuries to be the same, but complications of care to be less. If no difference between injury rates is found, we hypothesise that both arms will be equivalent in resource utilisation (ICU and hospital bed days, investigations ordered, interventions required).

## Methods/Design

This protocol adheres to the SPIRIT statement (www.spirit-statement.org). The Gold Coast Hospital and Health Service Human Research and Ethics Committee approved the study including informed consent processes as outlined under approval number HREC/14/QGC/79.

### Study design

This will be a multi-centre, cluster-randomised, controlled clinical intervention trial. The trial will compare two practices of tertiary survey performance: standard (routine) practice and standard practice with additional formalised trauma tertiary survey completion. This protocol was developed by a small group of experts in the field of tertiary survey in trauma, (including Emergency Physician and Trauma Surgeon) and methodology (Evidence-based medicine, statistics, health economics).

### Study setting

This trial is to be conducted in approximately 16 trauma receiving hospitals across Australia in at least 4 states: Queensland, New South Wales, Victoria and Western Australia. Participating hospitals do not have a dedicated trauma service or formalised process for review of admitted trauma patients.

### Study subjects - patients

All multi-trauma patients admitted to hospital for at least 24 hours will be prospectively identified using and Emergency Department Information System (EDIS or equivalent) and are eligible for recruitment if they meet the inclusion criteria based on previous work [15,16].

### Inclusion criteria

Inclusion criteria as used in previous studies [15,16] are as follows:16 years and olderAdmitted for at least 24 hours (since TTS can be performed up to 24 hrs) and any of the following:Injuries in two or more body regionsHigh impact mechanism (high speed motor vehicle collision, pedestrian versus car, fall from >1.5 meter)Chest or abdominal injuriesFractured neck of femur under the age of 65 years.

Informed consent for 1, 6 and 12-month telephone follow-up interviews will be obtained from the patient or proxy within 24 hours of enrolment.

### Randomisation

Participating hospitals (clusters) will be 1:1 randomised to either immediate (Group 1) or delayed (Group 2) introduction of TTS (Figure 1), using computer-generated random number function. Group 1 will implement formalised TTS in the first 12 months, with continuation of formalised TTS in the second 12 months. Group 2 hospitals will continue routine trauma care in the first 12 months followed by implementation of formalised TTS in the second 12 months. A statistician not involved with the data collection will be involved to conduct the randomisation. Results of the randomisation will be communicated to the operations manager of the study, who will inform the participating hospitals of the allocation. All patients of individual hospitals will receive the same treatment arm.

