### Statistical analysis and sample size

The primary analysis will be by intention-to-treat (ITT). Per-protocol analyses will also be performed, based on all patients completing 1, 6 and 12 months follow-up. Based on our prospective study [16], comparing routine care with the formalised TTS group, we anticipate a decrease in post discharge (Type III) injuries from 14% to 9%. We foresee this will be accompanied by an increase of in-hospital injury detection (missed injury Type I and II combined) from 4% to 9%.

The sample size for a cluster-randomized trial requires adjustment of the number of patients that a corresponding individually randomized trial would have needed. This is due to variation between the clusters, and results in a correction using the intra-cluster correlation coefficient (ICC) [21]. Using an alpha of 0.05 and a power of 0.80, a sample size of 638 patients per group, with 1-year follow-up completed, would be required if individually randomised. Our previous study [17] achieved a telephone follow-up rate of 40% at 6 months. Extrapolating a similar conservative follow-up rate at 12 months, a total of 3,190 patients will be required (1,595 for each cohort) to answer the primary hypothesis. To separately answer a before-and-after comparison in Group 2 hospitals a similar sample is required. This results in a sample of 6,380 patients, with complete 1-year follow-up in at least 2,552. Since approximately 0.4% [22] of all ED presentations consist of multi-trauma patients, approximately 1,600,000 ED presentations will be required. For an approximate 24-month recruitment period, this equates to 16 hospitals that have an average annual census of 50,000 presentations. Based on this sample size, the maximum ICC that can be present before the power of the study is reduced below 80% is dependent on cluster size and numbers and presented in Table 3*.*

**Table 3 Tab3:** **Approximate maximum intra-class correlation (ICC) for various cluster sizes and number of intervention hospitals to answer primary hypothesis**

**Number of intervention (and control) hospitals**	**Average size of cluster**	**Maximum ICC to have 80% power to detect 5% difference**
8	400	0.01
15	400	0.02
21	400	0.03
9	300	0.01
15	300	0.02
22	300	0.03
10	200	0.01
16	200	0.02
23	200	0.03

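### About 16 hospitals are allocated 1:1 with no stratification or constraint stated, so a sizeable chance imbalance between arms is possible and could be cheaply reduced before allocation

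*Protocol article*

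**What the plan says.** The Protocol article, Randomisation, states: "Participating hospitals (clusters) will be 1:1 randomised to either immediate (Group 1) or delayed (Group 2) introduction of TTS". The allocation is made "using computer-generated random number function". A statistician outside the data collection conducts it, and the operations manager passes the result to the sites. No balancing factor, block, matching or constraint is named there or elsewhere in the article.

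Study setting describes the clusters as "approximately 16 trauma receiving hospitals across Australia in at least 4 states" and limits the mix: "Participating hospitals do not have a dedicated trauma service or formalised process for review of admitted trauma patients". The sample-size section gives hospital size only as an average: "16 hospitals that have an average annual census of 50,000 presentations". The same section plans for a fall in Type III missed injury from 14% to 9%, and takes an average ICC of 0.01 from a study of trauma-receiving hospitals. Table 3 also covers ICCs of 0.02 and 0.03.

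Time schedule of enrolment has Group 1 introduce the intervention at the start of the trial. Only Group 2 has a year of routine care beforehand. Trial status reports that recruitment has not begun.

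**The concern.** With about eight hospitals in each arm, a random draw does not reliably balance hospital-level characteristics. Differences between the arms in background missed-injury rate, case mix or existing TTS practice then enter the primary comparison directly. Because no period before the intervention is described for Group 1, the arms cannot be compared on their prior Type III rates, nor adjusted for them. If a 5-point effect, or no effect, were observed, a reader would find it hard to judge how much of it reflected which hospitals fell into which arm. Restricting the allocation is the usual protection. It has to be built in before the draw.

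**Working it through.** **Inputs from the article.** Rates 14% and 9%; two-sided alpha 0.05; power 0.80; 638 followed patients per group; 40% follow-up; ICC 0.01; about 16 hospitals allocated 1:1, taken as 8 per arm.

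**The plan's own figure.** The pooled-variance formula for two proportions is n = [1.96·√(2·0.115·0.885) + 0.842·√(0.14·0.86 + 0.09·0.91)]² / 0.05² = 637.9, or 638 per group. Then 638/0.40 = 1,595 per cohort and 3,190 in total. The stated figures reproduce.

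**Chance difference between arms from hospitals alone.**
- Between-hospital SD = √(ICC·p·(1−p)) = √(0.01·0.14·0.86) = 0.0347, or 3.5 points.
- SD of the difference between two arm means of 8 hospitals = 0.0347·√(2/8) = 0.01735, or 1.7 points.
- 95% range = ±1.96·1.735 = ±3.4 points, which is 3.4/5 = 68% of the target effect.
- P(|difference| > 2.5 points) = 2·[1 − Φ(0.025/0.01735)] = 15%.

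| ICC | SD of difference (points) | 95% range (points) | P(> 2.5 points) |
|---|---|---|---|
| 0.005 (assumed) | 1.2 | ±2.4 | 4% |
| 0.01 (plan's value) | 1.7 | ±3.4 | 15% |
| 0.02 (Table 3) | 2.5 | ±4.8 | 31% |
| 0.03 (Table 3) | 3.0 | ±5.9 | 41% |

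**Illustration by state.** The article does not give the spread of hospitals over states. If it were four in each of four states (assumption), enumerating all 12,870 possible 8:8 splits shows that 24% leave at least one state wholly in one arm. Only 10% give 2:2 in every state.

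**What balancing and adjustment could remove.** If the factors explain a share R² of between-hospital variance, the SD becomes 1.735·√(1−R²). No value of R² is in the article, so a range is assumed.
- R² = 25%: SD 1.50 points, 95% range ±2.9.
- R² = 50%: SD 1.23 points, 95% range ±2.4.
- R² = 75%: SD 0.87 points, 95% range ±1.7.

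**Power.** With 638 followed per arm in 8 hospitals, about 80 per hospital, the design effect is 1 + 79·ICC. The standard error is √[(0.14·0.86 + 0.09·0.91)/638 × design effect], and power comes from the noncentral t distribution. An R² of 30% or 50% is treated as lowering the ICC from 0.01 to 0.007 or 0.005.

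| Residual ICC | Design effect | Degrees of freedom | Power |
|---|---|---|---|
| 0.01, no adjustment | 1.79 | 14 | 50% |
| 0.007, two df used | 1.55 | 12 | 54% |
| 0.005, two df used | 1.40 | 12 | 59% |
| 0.007, five df used | 1.55 | 9 | 52% |
| 0.005, five df used | 1.40 | 9 | 56% |

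Five df corresponds to four states entered as categories (3), census (1) and baseline TTS rate (1).

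**The case against.** Simple 1:1 cluster allocation is valid. The 1.7-point SD is the ordinary between-cluster variance expressed on another scale, and the plan already recognises that variance through the ICC and Table 3. A correct cluster analysis would carry it in the standard error. A random number function can also serve a stratified list, and the article condenses a fuller protocol.

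Much of this stands, and it limits the point in five ways.

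- **Not bias.** A reader might infer that the allocation biases the trial. It does not: over repeated draws the imbalance averages to zero. The remaining worry is that the chi-square test named in the article does not carry this error. At about 80 followed patients per hospital and ICC 0.01, its actual type I error would be about 14%. That is a defect of the analysis, not of the allocation.
- **Hospitals not yet fixed.** A reader might infer that all hospitals are already known. The article says only approximately 16, and funding is awaited. Confirming them before the draw is a condition of the fix.
- **Heterogeneity is inferred.** Excluding hospitals with a dedicated trauma service narrows the mix, and only an average census is given. The figures above rest on the plan's ICC and not on any description of the hospitals.
- **Power is not restored.** A reader might expect balancing to rescue power. The 50% starting point comes from the sample size. Part of the gain would also come from covariate adjustment after a simple draw. Adjusting for many factors erodes the gain by using up degrees of freedom.
- **Existing TTS rate is not free.** The roughly 25% figure is the team's own descriptive data. Hospital-specific rates would need a record audit at every site that does not already hold them.

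The appeal to condensation carries less weight. The article does describe the procedure: ratio, unit, method, who draws and who is told. The point is an improvement on that stated method, not a complaint about a missing detail.

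**Conclusion.** The point holds as a worthwhile design improvement, not as an error that invalidates the trial. On the plan's ICC of 0.01 and 14% rate, with 8 hospitals per arm, the chance difference in underlying rate has an SD of 1.7 points and a 95% range of ±3.4 points, with a 15% chance of exceeding half the 5-point target. These figures assume approximately normal hospital effects and equal arms; they grow at the larger ICCs in Table 3 and shrink if the ICC is below 0.01. The state-split figure and the share of variance that balancing would remove are illustrations, since the article gives neither the distribution of hospitals nor any R². The expected gain in power is a few points, from about 50% to 54-59% with two df used, or 52-56% with five. The stronger argument for the change is a comparison that is easier to believe when no Group 1 pre-intervention data are described.

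**What to change.** Once the participating hospitals are confirmed, have the independent statistician replace the plain draw with stratified or covariate-constrained randomisation, with equal numbers per arm stated explicitly. Balance on facts that need no new data collection: state or region, and annual ED census or expected multi-trauma volume. Add the existing TTS rate only where sites already hold it. Analyse the primary outcome at cluster level, or with an equivalent cluster method suited to few clusters, and account for the balancing factors with one or two degrees of freedom, for example by grouping states into regions.

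The cost is small: a few hospital facts, a short allocation program, and one or two of the 14 degrees of freedom. The real constraint is timing. All hospitals must be confirmed before the draw, so a site that joins late cannot simply be added. As recruitment has not begun, the change can still be made.

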**Figure 1 Fig1:**
[figure not shown]
Group allocation, randomisation and timeline.

### Informed consent

Individual participants will be asked to consent to follow-up, but not to allocation. Prior to these questions being asked, a brief explanation of the study will be given (patient information sheet); however, we will seek permission to provide limited disclosure to the patient. Specifically, we do not plan to advise them of the study while they are in the ED/hospital, for the following reasons:Patients *will not be individually randomised* and will receive management that is standard practice or standard practice with a formalised TTS.Limited disclosure will help to avoid potentially confounding variables.Risk to the patients in all parts of the study is negligible.Patients are not required to participate in any way whilst in hospitalThere is little reason to believe that patients would decline participation. In fact, <3% of patients declined participation in our previous study [16].

